### Intervention Description and Model Validation

The intervention is conceptualized as a work system comprising the following three parts: an AI model that predicts clinical deterioration, a mechanism for delivering the model predictions to clinical teams, and a multidisciplinary workflow driven by physicians and nurses. The clinical deterioration prediction model, the clinical deterioration index (CDI), was developed by Epic Systems Corporation and built into its EHR platform. The CDI is a logistic regression that runs every 15 minutes for all hospitalized patients using the most recent available clinical data of 31 physiological measures captured in the EHR and generates a score between 0 and 100, with higher scores indicating an increased risk of clinical deterioration as defined by any one of the following: ICU transfer, inpatient code, RRT event, or death. Between January 2020 and May 2020, the model was prospectively validated on 6232 hospital encounters of patients admitted to the implementation site for its accuracy in predicting ICU transfer or RRT event within 6-18 hours of the prediction, which was deemed by the clinical stakeholders to be an appropriate time interval that would allow for a meaningful clinical response. Of these 6232 encounters, 152 (2.44%) were unplanned ICU transfers and RRT events. The area under the curve was 0.70, and a model score threshold of 65 (out of 100) was chosen to maximize the positive predictive value and sensitivity of 0.20. Of note, this validation strategy was an enhancement of the vendor’s validation, which reported model accuracy in predicting the outcomes *without* the 6-hour to 18-hour time lag; this was thought to not be clinically meaningful because a model predicting an event to occur within the next 6 hours would not provide sufficient time for a clinical response to be effective.

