**Figure 2 figure2:**
[figure not shown]
Stepped wedge design for the implementation and evaluation of a clinical deterioration model and workflow. Under *Baseline* column, blue shading includes data from the 10 months prior to the roll-out of the intervention for all 6 participating units (60-unit months for analysis). Under *Month* column, yellow shading represents stage 1 and the physician-only intervention for the physician-nurse team (25-unit months for analysis). Under *Month* column, green shading indicates stage 2 and the intervention for the physician-nurse team (41-unit months for analysis).

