### Analysis

#### Quantitative Analysis

The primary aim is to assess the impact of the physician-only and team interventions on the unit-level clinical outcomes compared with baseline data. The secondary aim is to explore how the intervention is implemented by describing the process outcomes that were developed and launched as part of the intervention-specific workflow. For these process outcomes, the differences between the physician-only and team interventions will be statistically evaluated because baseline data will not be available for these outcomes. Poisson regression will be applied for unit-level count outcomes to determine the differences among the three phases of the study (baseline, physician-only, and team), followed by pairwise comparison. A multilevel, mixed-effects model will be used for patient-level outcomes to include the covariate unit to account for nesting. The level of statistical significance will be set at *P*<.05.

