#### Power Calculation

On the basis of the aforementioned study design, we assessed the minimum effect size of the team intervention that can be detected with sufficient power (>80%). The percentage reduction in the number of RRT activations in response to adverse events per unit per month (RRT/unit/month) was chosen as the effect size measure because it is the most proximal of the clinical outcomes to the implemented workflow. As shown in Figure 2, our design provides a baseline period of 60 unit months and a team intervention period of 41 unit months. Assuming that the occurrence of RRT events follows a Poisson process, we conducted simulation studies with 10,000 replications to estimate the power curves using the following three scenarios. The first scenario assumes a mean rate of 4.5 RRT/unit/month during the baseline period for all 6 units. The second and third scenarios assume the following heterogeneous mean rates across the 6 units: 3.5 RRT/unit/month for 2 units, 4.5 RRT/unit/month for 2 units, and 5.5 RRT/unit/month for 2 units. In scenario 2, we assume that the team intervention is introduced to the units with lower rates at baseline first and the higher-rate units last, whereas in scenario 3, we assume the opposite. All scenarios use a two-sided α set at .05. Figure 3 shows the power curves for each scenario: scenarios 1, 2, and 3 indicate 80% power to detect a reduction in the RRT event rate of approximately 25%, 18%, and 30%, respectively.

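### The stated models compare each intervention phase with a non-concurrent baseline without a case-mix term, so a change in patient acuity would be read as an intervention effect

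*Protocol article*

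**What the plan says.** The Quantitative Analysis section defines the main comparison: "The primary aim is to assess the impact of the physician-only and team interventions on the unit-level clinical outcomes compared with baseline data". For the counts it states: "Poisson regression will be applied for unit-level count outcomes to determine the differences among the three phases of the study", followed by pairwise comparisons. For patient-level outcomes it states: "A multilevel, mixed-effects model will be used for patient-level outcomes to include the covariate unit to account for nesting". Unit is the only covariate named, and no severity, case-mix or calendar-time term appears.

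Other sections bear on this:

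- **Implementation Strategy:** stage 1 goes live across all 6 units, and only stage 2 is staggered.
- **Study Design:** the baseline is the 10 months before implementation, and month 1 is March 2021.
- **Sample:** unit-level outcomes include all patients admitted to the units. Patient-level outcomes include only patients who reach CDI≥65 during the stay.
- **Outcomes:** RRT activations, codes, ICU escalations, deaths and readmissions are unit-level. Length of stay is the only clinical outcome at patient level.
- **Intervention Description and Model Validation:** the CDI "runs every 15 minutes for all hospitalized patients using the most recent available clinical data of 31 physiological measures captured in the EHR", and it was validated at the site on encounters from January to May 2020.

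**The concern.** Once stage 1 begins, no unit remains at baseline. The staggered rollout gives concurrent information on team versus physician-only, but none on either phase versus baseline, which is the primary contrast. Baseline patients are different people treated in different months.

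A phase-only Poisson model attributes any difference in event rate between those months to the phase. If patients admitted in the intervention months are less sick, RRT, ICU, code and death counts fall without any intervention effect. If they are sicker, a real benefit is hidden. A unit term does not remove this, because acuity can change within a unit over time. Nor does a patient-volume denominator, because the same number of patients can be more or less sick.

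The primary clinical conclusion is at stake. An acuity marker computed for all inpatients exists at the site, yet the stated models do not use it.

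**Working it through.** **Inputs from the Power Calculation section**

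- Exposure: "our design provides a baseline period of 60 unit months and a team intervention period of 41 unit months".
- Rate: "The first scenario assumes a mean rate of 4.5 RRT/unit/month during the baseline period for all 6 units".
- Test level: "All scenarios use a two-sided α set at .05".

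**Input assumed:** the acuity-driven multiplier m on the event rate. The protocol gives none, so a range is shown.

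**Formula.** Expected events are E0 = 60 × 4.5 = 270 at baseline and E1 = 41 × 4.5 × m = 184.5m in the team phase. SE = √(1/E0 + 1/E1) and z = ln(m)/SE. The rejection probability is Φ(−1.96 − z) + Φ(−1.96 + z).

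**Step 1: reproduce the plan's own figure.** For scenario 1 with a true 25% reduction, m = 0.75 and E1 = 138.4. SE = √(1/270 + 1/138.4) = 0.1045 and z = −0.2877/0.1045 = −2.75. Power is 0.79 by formula and 0.795 in 200,000 simulated replications. The plan states 80% power at approximately 25%, so the test used here matches it. Scenarios 2 and 3 depend on the unit schedule in Figure 2, which is not shown, and are not used here.

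**Step 2: no intervention effect, acuity shift only, team versus baseline**

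| Assumed rate change | E1 | SE | z | Rejection, formula | Rejection, simulated |
|---|---|---|---|---|---|
| none | 184.5 | 0.0955 | 0 | 5.0% | 4.9% |
| −5% | 175.3 | 0.0970 | −0.53 | 8.3% | 8.1% |
| −10% | 166.1 | 0.0986 | −1.07 | 18.7% | 18.4% |
| −20% | 147.6 | 0.1024 | −2.18 | 58.7% | 59.3% |
| +10% | 203.0 | 0.0929 | +1.03 | 17.6% | 17.7% |

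When the rate falls, nearly all of the excess rejections appear as benefit. When it rises, they appear as harm. For physician-only versus baseline (25 unit-months, Figure 2 caption), the simulated rates are 14.1% at −10% and 45.1% at −20%.

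**Step 3: masking.** With a true 25% reduction and a 10% acuity-driven rise, the apparent multiplier is 0.75 × 1.10 = 0.825, a 17.5% reduction. E1 = 152.2, SE = 0.1014 and z = −1.90. Power is about 0.48 instead of 0.80.

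**Step 4: what adjustment could recover.** If the acuity shift were captured completely, for example by a correct offset, the simulated false-positive rate returns to 4.9–5.0% for shifts of −20%, −10% and +10%. This is the best case. Real covariates capture only part of a shift.

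**Step 5: how a shift could arise.** The validation figures are 152 events in 6232 encounters (2.44%), with positive predictive value and sensitivity both 0.20. True positives are 0.20 × 152 = 30.4 and flagged encounters are 30.4/0.20 = 152 (2.44%). Risk in the unflagged is 121.6/6080 = 2.0%. If the flagged share halved (an assumption), overall risk would be 0.0122 × 0.20 + 0.9878 × 0.020 = 2.22%, a 9% fall. For m = 0.91, SE = 0.098 and z = −0.96, giving about 16% rejections. These inputs describe ICU transfers and RRT events among patients admitted to the site, so applying them to RRT activations in the six units is only indicative.

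**The case against.** The strongest reply is that this is a short journal summary. Naming unit explains how clustering is handled; it is not a closed list of covariates, and a full analysis plan may add case-mix terms. That stands as a limit: one cannot conclude that no adjustment will ever be made. It does not remove the point, because the article states the models for its primary contrast, and run as stated they are biased whenever case mix shifts.

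Other objections that stand:

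- The CDI≥65 restriction gives partial severity control for length of stay. It does not touch the unit-level outcomes, which carry the primary aim, and severity and comorbidity can still vary above the threshold.
- The protocol does not say that CDI scores are held for every baseline month. This is inferred from the January–May 2020 validation and from the need to identify baseline patients with CDI≥65. Age, admission source and diagnosis are not named among the extracted items either.
- CDI at first crossing is bounded below at 65, so it adds little as a covariate.
- With an area under the curve of 0.70, the CDI leaves much risk unexplained.

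A reader might also infer that adjustment would tighten the confidence intervals for the counts. It would not: with an expected-events offset, the standard error of the log rate ratio is still √(1/E0 + 1/E1).

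**Conclusion.** The point holds as a weakness in the stated analysis of the primary contrast. The comparison with baseline is not concurrent, unit-level outcomes include all patients, and neither stated model carries a case-mix term. Acuity-driven changes smaller than the 18–30% reductions the study is powered to detect would materially distort the result: about 8% false positives at a 5% fall, 18% at 10% and 59% at 20%, with power down to about 0.48 if a 10% rise offsets a true 25% reduction.

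These sizes rest on the scenario 1 rate, Poisson variation and assumed shifts. A reader might infer that acuity did change between phases; the protocol contains no evidence of this. Nor does it support a claim that adjustment would make the before–after contrast unconfounded: residual confounding and calendar-time effects would remain. The expected gain is less bias in the phase comparisons. Better precision may be expected only for length of stay. The change should be made, but the study does not stand or fall on it.

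**What to change.** Prespecify case-mix adjustment using values fixed on arrival in the unit and before any alert: first CDI on the unit, age, admission source and diagnosis group. Later CDI values should not be used, because the intervention may change them. First confirm that these fields are held for the baseline months.

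- **Unit-level counts:** fit a patient-level risk model in the baseline phase, sum the predicted risks per unit-month and use log(expected events) as the Poisson offset. Alternatively, enter unit-month mean arrival acuity as a covariate. Use a simpler covariate set for rare outcomes such as codes and deaths.
- **Length of stay:** add the arrival covariates to the mixed model beside unit, rather than relying on CDI at first crossing.
- **Reporting:** give the unadjusted result as a sensitivity analysis, and state that residual and calendar-time confounding remain. Case-mix adjustment does not replace a calendar-time term.

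The cost is analysis-plan wording, one extra modelling step and a few further EHR fields. If those fields are confirmed for the baseline months, no new data collection is needed. The covariates should be fixed before outcome results are seen.

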### Setting

The intervention will be implemented in 6 primary general medicine adjustable acuity units at a quaternary academic hospital in the United States. The hospital has 605 beds, and most general medicine patients are cared for in 6 primary general medicine units. Each unit is served by physician teams, each with an average census of 12 and a maximum census of 20. The physicians spend most of their day rounding in many units and access the EHR through mobile devices, whereas the nurses spend most of their day in 1 unit working on a mobile desktop computer. These work setting characteristics were a key consideration in the intervention, implementation strategy, and study design.

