### Implementation Strategy

The intervention implementation will be split into two stages to assess its impact when offered to the physicians only (stage 1) and later to the entire physician-nurse team (stage 2). In stage 1 (yellow shading in Figure 2), the three alert modes will be delivered only to the physicians for patients across all 6 patient care units, and subsequent workflows will be initiated only by the physician.

In stage 2 (green shading in Figure 2), the alert modes will also be delivered to the nurses on the clinical teams, and either the physician or the nurse on the team can initiate the downstream workflow, thus creating a team approach to identifying and managing clinical deterioration. Nurses are to perform a parallel clinical validation of the alert and contact the physician to conduct the aforementioned risk-of-deterioration huddle. Thus, assessment of the risk and initial steps to manage deterioration can be initiated by either the physician or the nurses in the team intervention model. Stage 2 will be rolled out in a stepwise manner to each of the 6 primary general medicine units.

Rolling out the intervention using a stepwise approach was chosen for pragmatic implementation and evaluation purposes. The physicians care for patients across all 6 patient care units, whereas the nurses are staffed based on individual units. For implementation practicality and patient safety, stage 1 (physician-only intervention) would thus be implemented across all 6 units, whereas the implementation of stage 2 (the addition of nurses) would be staggered by the patient care unit so that the nurses in each unit can be trained in the new workflow together. This implementation strategy also allows us to evaluate the additive impact of delivering AI predictions to the entire physician-nurse team using a stepped wedge design.

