### Outcomes

The clinical outcomes will be derived from data extracted from the patients’ EHRs related to inpatient hospital stay and up to 30 days after discharge to capture readmission. Using these data, the outcomes will be calculated and expressed at either the unit or patient level, as described herein. To facilitate generalizability and comparisons with other outcomes, the following outcomes, which are commonly assessed in other interventions for clinical deterioration [2,5,16], will be evaluated to address aim 1:

Number of RRT activations in response to adverse events per unit per month (RRT/unit/month; unit level)Number of code events per unit per month (codes/unit/month; unit level)Number of ICU escalations per unit per month (ICU/unit/month; unit level)Mortality per unit per month (deaths/unit/month; unit level)Readmission rates (30-day rates) per unit per month (30-day readmissions/unit/month; unit level)Length of stay in acute inpatient setting (patient level nested in unit)

We will also explore the process outcomes informed by the SEIPS 2.0 model and the implementation outcomes described by Proctor et al [17] to assess the ways in which the model and workflow changed the work system and, subsequently, the work processes (aims 2 and 3). Where possible, these outcomes will be derived from the patients’ EHRs and a secure text messaging platform to minimize the required data reporting by clinicians. A focused chart review of a subsample of patients will also be conducted for data not extracted through the methods described previously. Examples of these processes include the following:

Completion of documentation in the EHR (unit/month; unit level)Number and type of staff engaged in the intervention workflow (patient level nested in unit)Actions taken by the team engaged in the intervention workflow (patient level nested in unit)Time elapsed between alert and completion of workflow procedures, including documentation (patient level nested in unit)

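### Patient-level outcomes are modelled with unit as the only named cluster, although physicians work across all six units; if physicians turn over during the study, the standard errors are too small

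*Protocol article*

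**What the plan says.** Under Quantitative Analysis, patient-level outcomes are given a multilevel mixed model "to include the covariate unit to account for nesting". The Outcomes section uses the same structure. It labels length of stay, the staff engaged, the actions taken and the time from alert to completion as patient-level measures nested in unit, for example "Number and type of staff engaged in the intervention workflow (patient level nested in unit". Quantitative Analysis commits to testing the process outcomes between the physician-only and team stages, with significance at P<.05. They have no baseline data.

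The clinical setting is described differently. Implementation Strategy: "The physicians care for patients across all 6 patient care units, whereas the nurses are staffed based on individual units". Setting: "The physicians spend most of their day rounding in many units", and "Each unit is served by physician teams, each with an average census of 12 and a maximum census of 20". In stage 1 only the physician starts the workflow. In stage 2 either the physician or the nurse may start it, and the nurse contacts the physician for the huddle.

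**The concern.** Nesting in unit suits the nurses, who belong to one unit. It does not suit the physicians, who cut across units. Three of the four patient-level outcomes named above describe how the clinical team responds to an alert, so patients of the same physician may be correlated even when they lie in different units. A model with unit alone treats them as independent.

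What is at stake is the precision of the physician-only versus team comparison, that is, the added value of bringing in the nurses, which is a stated purpose of the design. If the physicians on service change over the 11 months, early physicians contribute more to stage 1 and later ones more to stage 2. Chance differences between them can then look like a stage effect, and the intervals are too narrow.

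**Working it through.** **The plan's own figure.** The article gives no power or precision figure for any patient-level outcome. Its only such figure concerns rapid response team (RRT) counts per unit-month. Scenario 1 can be checked with a Wald test on the log rate ratio: ln 0.75 = −0.2877; SE = √(1/(60×4.5) + 1/(41×4.5×0.75)) = √(1/270 + 1/138.4) = 0.1046; ratio 2.752; power = Φ(2.752 − 1.960) = 78.6%, against the stated 80% or so. It reproduces, and the patient-level model does not enter it.

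**Inputs from the article.** Six units; 11 intervention months; 25 stage 1 and 41 stage 2 unit-months (25 + 41 = 66 = 6 × 11).

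**Assumptions.**
- Alert volume: about 30 a month. The validation had 152 events in 5 months. Reading positive predictive value and sensitivity both as 0.20, flagged patients = 152 × 0.20 / 0.20 = 152, or 152/5 = 30.4 a month. Over 11 months this is about 330.
- 6 or 10 physician teams. The article gives no number.
- Physician ICC of 0.05, 0.10 or 0.20. The article gives none.
- Physicians either stay throughout or are replaced every month. The article says neither.
- Roll-out (the figure is not shown): stage 1 months per unit of (1,2,3,5,7,7) or (2,3,4,5,5,6), each summing to 25.

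**Rough calculation under monthly turnover.** Patients per team per month: 30/10 = 3 or 30/6 = 5. If each team-month fell wholly in one stage and all were of equal size, the variance would be inflated by D = 1 + (m − 1) × ICC, and the type I error of a nominal 5% test would be 2Φ(−1.96/√D).

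| ICC | D (m = 3; 5) | Type I error, formula | Type I error, simulation |
|---|---|---|---|
| 0.05 | 1.1; 1.2 | 6.2%; 7.4% | about 5–7% |
| 0.10 | 1.2; 1.4 | 7.4%; 9.8% | about 7–10% |
| 0.20 | 1.4; 1.8 | 9.8%; 14.4% | about 8–14% |

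**Simulation.** Stage 1 versus stage 2, stage and unit terms only, no true stage effect. With 1,500 replications the Monte Carlo standard error at a rate of 7% is √(0.07 × 0.93/1500) = 0.7 percentage points. The formula and the simulation agree.

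**Sensitivity to volume.** A separate simulation with 12 teams, monthly turnover and 5 or 20 patients per unit per month gave 6–10% at ICC 0.05 and 7–16% at ICC 0.10. The upper ends belong to 20 per unit, four times the volume implied above (30/6 = 5 per unit).

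**Stable physicians.** When the same physicians see patients in all units throughout, the unit-only model rejected in about 3–6% of simulated trials. In the separate simulation the ratio of true to model standard error was 0.98 to 1.03 at ICC up to 0.10.

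**Does a physician term repair it?**
- Random effect for an identifier that changes with the people: about 3–6% under turnover, and 4–5% with stable physicians at ICC 0.10.
- Standing team label while the members change (fitted as fixed effects): 7.5–9.3% at ICC 0.10 and 9.3–13.6% at 0.20, so no real gain.
- Calendar month instead: 4.6–5.3%.

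**The case against.** Four arguments weigh against the point.

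- **Turnover is not documented.** This stands. The interview sample includes residents, interns and fellows, which makes turnover plausible, but no rotation schedule is given. Without turnover the unit-only model is about right, so the effect must be stated as conditional.
- **A condensed article may leave the random-effects structure to a fuller plan.** This stands in part. Such a plan may contain the term. But the article is not silent: it names one structure in two sections, and its own description of physician work does not fit it.
- **The simulated problem is partly one of time.** This also stands. The inflation arises because the physicians on service differ from month to month and month is correlated with stage, which is why a month term also removes it. A loosely chosen team label would not help.
- **Only secondary outcomes are touched.** Correct. The primary aim concerns unit-level outcomes.

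A reader might go further and infer that physicians are the main source of clustering, or that team differences fall mostly between the two stages. The article supports neither. It gives no variance figures, and unit is both the roll-out cluster and the nurse cluster. Under the two assumed schedules, 25 − 6 = 19 and 25 − 12 = 13 of the 25 stage 1 unit-months lie in months when both stages run, so physicians who cross units then see both.

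**Conclusion.** The mismatch is real: the patient-level model names unit alone, while the article's own account makes physician crossed with unit. Its consequence is conditional. With stable physicians, type I error is about nominal. With monthly turnover and about 30 alerts a month, it rises only slightly at an ICC of 0.05 and reaches 8–14% at 0.20. The ICC, the number of teams, the turnover and the roll-out schedule are assumptions, and the alert volume is an inference from the validation figures. These sizes are for stage 1 versus stage 2; none is offered for length of stay against baseline. The point is minor and leaves the unit-level primary aim and the power calculation intact.

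**What to change.** In the mixed model for all patient-level outcomes (Quantitative Analysis), add a random effect, crossed with unit, for the treating physician, or for the team within its service block, recorded when the patient first crosses the alert threshold. The identifier must change when the people change; a standing team name is not enough. Apply a small-sample correction to the stage comparison and report the unit-only model as a sensitivity analysis.

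The cost is one more field from the health record, one model term and slightly wider intervals. If physicians prove stable, the added term costs almost nothing.
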